#### Secondary outcome

A standard socio-demographic and medical history form (SDMH) will be used to collect patients’ background data on ethnicity, age, marital status, religion, education level, employment status, income level, travel time to hospital, insurance status, mental health status, family history of cancer and use of traditional healer. The patients’ medical records will also be reviewed to obtain data on type and stage of cancer and type of treatment.

Patient knowledge will be assessed using the Breast Cancer Knowledge Test (BCKT). The BCKT is a 20-item questionnaire that was developed and tested to determine (a) general knowledge of breast cancer; and (b) the relationship between the knowledge of breast cancer and utilization of screening practices. The BCKT consists of 2 subscales; one subscale of 12 items to measure general knowledge and one subscale consisting of 8 items to measure knowledge of curability. In the first section, item number 3 about the breast cancer prevalence was adjusted with the actual Indonesian prevalence rate. The total score ranged from 0 to 20, with higher scores indicating higher breast cancer knowledge. The BCKT has an acceptable reliability coefficient (α = 0.69). The Breast Cancer Knowledge Test (BCKT) has been translated into Indonesian using the forward-backward translation method [24].

Symptoms of anxiety and depression will be measured with the Hospital Anxiety and Depression Scale (HADS). The HADS is a 14-item self-report questionnaire that was developed to assess psychological distress in people with medical illness. It consists of 2 subscales: 7 items to measure anxiety (HADS-A) and 7 items to measure depressive symptoms (HADS-D). Psychometric properties of the Indonesian version of the HADS were adequate, with values of Cronbach’s coefficient (alpha) being 0.77 and 0.74, respectively [13].

Quality of life will be measured using the WHOQOL-BREF ([25]; in the Indonesian version with a 4 week-time frame). This tool is a self-report questionnaire that consists of 26 items and each item represents one facet of life that is considered to have a contribution to a person’s quality of life. Two items measure quality of life and health satisfaction in general. Twenty-four items measure four broad domains, namely physical health (7 items), psychological health (6 items), social relationships (3 items) and environmental (8 items). The WHOQOL-BREF has been validated, and indicates high validity and reliability for measuring the quality of life among the elderly [26]. We will also use the EQ-5D 5L to measure health-related quality of life [27]. EQ-5D 5L is based on a descriptive system that defines health in terms of 5 dimensions: mobility (MO), self-care (SC), usual activities (UA), pain/discomfort (PD), and anxiety/depression (AD). Each dimension has 5 levels: no problems, slight problems, moderate problems, severe problems, and extreme problems/unable. This descriptive system is then followed by a self-rating of overall health status on a visual analogue scale (EQ - VAS) ranging from 0 (“the worst health you can imagine") to 100 (“the best health you can imagine"). EQ-5D 5L has been validated in diverse patient populations in numerous countries [28]. The official Bahasa Indonesia version of the EQ-5D 5L will be used; provided by the EuroQol Group [29].

Feedback from participants on the intervention material package will be measured using The Intervention Material Feedback Form. This instrument has been developed by the researchers. Finally, treatment delay will be measured at the follow-up measurement by asking the patient with a positive diagnosis if she has started her treatment at the hospital. This will also be checked with the hospital records.

### Analysis plan

Demographic characteristics will be summarized using descriptive statistics, including percentages for categorical data, and means and standard deviations for continuous data. The descriptive statistics will be tabulated and presented graphically. Hierarchical linear modeling (HLM) will be employed to evaluate potential changes in the Diagnostic Delay Questionnaire scores over time. In this study, a three level model will be used with repeated measures nested in person, and persons nested in clusters. Time (pre, post, follow-up) will be considered as level 1, the individual persons will be considered as level 2 and the clusters (intervention-control group) will be considered as level 3. HLM analysis using a similar model will also be carried out to evaluate potential changes in the scores of secondary outcomes: Quality of Life (WHOQOL-BREF and EQ-5D 5L), HADS, and BCKT respectively. HLM analysis will be carried out separately for each phase before and after crossover. Demographic variables will be entered as additional predictors including SES, educational levels, and patients’ locations to explore potential impact on the effect of the interventions.

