## Abstract

**Background:**

Breast cancer (BC) is the most frequent cancer occurring in women across the world. Its mortality rate in low-middle income countries (LMICs) is higher than in high-income countries (HICs), and in Indonesia BC is the leading cause of cancer deaths among women. Delay in breast cancer diagnosis negatively impacts cancer prognosis. Only about 30% of patients who come to the hospital to check on their breast abnormalities, continue thorough examination to biopsy to get a diagnosis based on the results of anatomical pathology. Many Indonesian women with breast cancer were already in an advanced stage when starting treatment. Therefore, delay in diagnosis is a serious problem that needs to be addressed. The present study will investigate whether our newly developed self-help psycho-educational programme, “PERANTARA”, for women with breast cancer symptoms is effective to reduce patient diagnosis delay in Indonesia.

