### Procedure

The healthcare professionals (oncologist or nurse) will inform eligible participants about the study (see Fig. 1). The research assistant will follow up to inform the patients about the details of the study and asks them for oral and written informed consent. Patients who agree to participate will be asked to fill in: (1) the socio-demographic and medical history form, (2) the World Health Organization Quality of Life - Assessment Bref (WHOQOL-BREF), (3) the European Quality of Life-5 Dimensions-5 Levels (EQ-5D-5 L), (4) the Hospital Anxiety-Depression Scale (HADS) Questionnaire, (5) the Breast Cancer Knowledge Test (BCKT). Participants who are illiterate will be giving an oral consent and a thumb print in lieu of a signature, in line with recommendations from WHO [23].

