### Instruments

#### Primary outcome

Diagnosis delay will be the primary outcome measure. This is defined as the time between the date of the first consultation at the hospital and the date of the definite breast cancer diagnosis based on pathological examination. This outcome will be measured using the Diagnostic Delay Interviewer Guide. This instrument has been developed by the researchers and consists of the following questions: (a) What was the date that you consulted with a doctor in the hospital?, (b) What was the date that you received the breast cancer diagnosis?, and if there was a consult delay (c) What were the reasons for delay? A distinction will be made between delay due to the patient and due to the doctor. This tool will be pilot-tested before the final data collection is done.

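### The primary outcome is one time-to-diagnosis interval per woman, but the plan analyses it as a score repeated at pre, post and follow-up, with no baseline measurement and no valid value for women still without a result

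*Protocol article*

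**What the plan says.** **Outcome.** Design and Primary outcome both define diagnosis delay as a duration. In the latter: "This is defined as the time between the date of the first consultation at the hospital and the date of the definite breast cancer diagnosis", with pathology as the standard for that diagnosis. The instrument asks for the date of the hospital consultation, then "What was the date that you received the breast cancer diagnosis", then the reasons for any delay. No scoring is described.

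**Analysis.** The Analysis plan says that "Hierarchical linear modeling (HLM) will be employed to evaluate potential changes in the Diagnostic Delay Questionnaire scores over time". The structure is three-level, with repeated measures within women within clusters, and "Time (pre, post, follow-up) will be considered as level 1". A similar model is planned for quality of life, HADS and BCKT. The Abstract also names HLM, to assess differential change over time.

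**Schedule.** The baseline list in Procedure begins "Patients who agree to participate will be asked to fill in: (1) the socio-demographic and medical history form" and continues with WHOQOL-BREF, EQ-5D-5L, HADS and BCKT. The Diagnostic Delay Questionnaire appears only at the post-assessment, 7 days after the intervention, and at the follow-up 12 weeks later.

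**Background figure.** The Abstract says that "Only about 30% of patients who come to the hospital to check on their breast abnormalities, continue thorough examination to biopsy".

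**The concern.** The stated model needs a quantity measured on each woman at three occasions. The stated outcome gives at most one completed value per woman, and none at the first occasion. The protocol names the outcome, the model and its time levels, and they do not fit together, so this is not a detail left to a later document.

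What is at stake is how women without a pathological result enter the primary comparison. If they are omitted, the comparison becomes mean delay among women who obtained a diagnosis. Obtaining one happens after randomisation and is something the programme is meant to bring about, so the two arms would be compared on differently selected women.

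**Working it through.** **1. Outcome against model**

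| Item | Outcome and Procedure sections | Analysis plan |
|---|---|---|
| Quantity | interval between two dates | score |
| Completed values per woman | at most 1 | repeated |
| Occasions | instrument given at 2 (post, follow-up) | 3 (pre, post, follow-up) |
| Value at pre | none: not in the battery, and entry precedes diagnosis | assumed present |

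By contrast, BCKT, HADS, WHOQOL-BREF and EQ-5D-5L are scheduled at all three occasions, so the repeated-measures structure fits them.

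**2. Women with no completed interval**

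Follow-up ends about 1 + 12 = 13 weeks after the intervention. The protocol gives no expected share diagnosed by then. If the background 30% applied: 0.30 × 106 = 31.8, about 32 women with a result and 74 (70%) without. If the share with a result were anywhere from 20% to 70%, between 85 and 32 women would have no completed interval.

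**3. The plan's own sample size**

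Participants gives 41 per group (power 0.80, two-sided alpha 0.05) without an effect size, so it can only be back-solved. Assuming a comparison of two means: d = (1.960 + 0.842) × √(2/41) = 0.62. That would describe a complete continuous outcome, not a censored interval.

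**4. What 106 women can detect with time to event**

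Schoenfeld formula, 1:1 allocation: minimum detectable HR = exp[(1.960 + 0.842) / √(events/4)].

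| Women followed | Share with event (assumed) | Events | Minimum detectable HR, 80% power |
|---|---|---|---|
| 106 | 20% | 21 | 3.4 |
| 106 | 30% | 32 | 2.7 |
| 106 | 50% | 53 | 2.2 |
| 106 | 70% | 74 | 1.9 |
| 82 (2 × 41) | 30% | 25 | 3.1 |

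With 32 events, power is about 50% for HR 2.0 and 21% for HR 1.5. Clustering and period are ignored, so these figures are optimistic.

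**5. How a diagnosed-only mean can mislead (illustration on assumed data)**

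Assume exponential times with 30% v 45% diagnosed by week 13, so HR = ln(0.55)/ln(0.70) = 1.68. Rates λ = −ln(1 − p)/13 are 0.0274 and 0.0460 per week.

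- Mean among the diagnosed, 1/λ − 13(1 − p)/p: 6.11 v 5.86 weeks, about 1.8 days apart.
- Restricted mean over all women, p/λ: 10.93 v 9.79 weeks, about 8 days apart.

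The two summaries answer different questions. This does not show that one analysis always has more power; see the objection.

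**The case against.** **The model could be fitted in some form.** With the instrument given twice, delay accrued to date could be modelled at post and follow-up. That is fair, and a reader who infers that the analysis cannot be fitted at all goes too far. But an undiagnosed woman's value is then fixed by the visit date, the pre level is still empty, and the two values are snapshots of one interval. The only informative value is the one at follow-up, which is one restricted delay per woman rather than a change over time.

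**The 30% is a background figure.** It has no time window and is not a planning assumption for this trial. A reader might infer that 70% of participants never reach biopsy, or that the analysis deletes the women with the longest delay. The protocol supports neither: some women may not need biopsy, and no rule for undiagnosed women is stated. How many are affected is therefore unknown. The mismatch does not depend on it.

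**Time-to-event analysis need not gain power.** This stands. In simulations with 53 per arm, clustering ignored, the exponential example in step 5 gives about 6% power for a t-test among the diagnosed and 37% for a log-rank test on all women (8% v about 90% for 30% v 60% diagnosed). Now assume instead that only a share of women have cancer, that their mean delay falls from 6 to 3 weeks, and that benign cases are censored at week 13. The ranking reverses: 25% v about 8% when the share is 0.3, and 59% v 41% when it is 0.8. The protocol favours neither model, so a claim of rescued power is unsupported.

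**Censoring every woman without a cancer diagnosis would be a new error.** This also stands. Participants are women with suspicious symptoms, and the event is a breast cancer diagnosis. A woman promptly biopsied with a benign result would count the same as one who avoided biopsy.

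**Conclusion.** The primary analysis as written does not fit the primary outcome and must be changed. Three parts rest on the text alone: one interval is modelled as a repeated score, the pre level has no measurement, and no completed delay can exist at entry. That a linear model of the interval has no valid value for women without a result follows directly.

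Their number is an inference: about 74 of 106 if the background 30% applied, and 32 to 85 over the assumed range. The argument for time to event is validity, namely keeping every randomised woman in the comparison and avoiding selection on a post-randomisation event. It is not a promise of more power.

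**What to change.** 1. Analyse diagnosis delay once per woman, as time from first hospital consultation to definite pathological result. Censor women with no pathological result at follow-up or last contact.
2. State how benign results count: either any definite pathological result, malignant or benign, is the event, or a benign result is a competing event. Do not censor benign cases as undiagnosed.
3. Use a model that accounts for hospital and period. Cox regression stratified by hospital with a period term is one option, but it leaves correlation within hospital-periods to be dealt with, and there are only four hospitals.
4. Report the cumulative proportion with a result and the restricted mean delay by arm.
5. Extend the record review, at present planned for treatment delay, to confirm the date of the pathological result.
6. Keep the repeated-measures HLM for BCKT, HADS, WHOQOL-BREF and EQ-5D-5L.

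**Cost.** Revised analysis wording and a small extension of the record review, since diagnosis dates now come from patient interview. The effect becomes a hazard ratio or restricted mean rather than a change in score. If any pathological result is the event, the outcome definition changes too. The power statement must be redone on expected events with an allowance for clustering, and it may show that 106 women detect only large effects.

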**Methods:**

A cluster-randomized controlled trial will be conducted in 106 patients in four hospitals in Bandung, West Java, Indonesia. Data will be collected at baseline (pre-assessment), 7 days after the intervention (post-assessment), and at 3 months (follow-up assessments). The primary outcome is delay in diagnosis and treatment. Secondary outcomes are breast cancer knowledge, anxiety and depression, and quality of life. Exploratively, adherence with treatment will be measured too. Data will be analysed by hierarchical linear modelling (HLM) to assess differential change over time.

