## Methods

### Design

The study will be a multicentre, cluster-randomized controlled trial (cRCT), with hospitals as the unit of randomisation (clusters). We will include four hospitals in Bandung, Indonesia that have agreed to participate in this study. Because of the limited number of hospitals, we will use a cross-over design in which in each hospital will be given PERANTARA or control (treatment as usual (TAU)) at successive periods. Because every hospital forms its own control, the cross-over design can produce results with a smaller sample size than required with a parallel design. The order in which the hospital receives PERANTARA is randomly determined. The study will compare the PERANTARA to TAU in women with suspected breast cancer. This study uses two predefined periods. In the first period, two hospitals will have the experimental group (the patient is given the intervention and TAU) and two other hospitals will have the control group (patients only receive TAU). In the second period, it is the other way around.

The primary outcome is diagnosis delay in terms of the time between the date of the first consultation at the hospital and the date of final breast cancer diagnosis based on pathological examination. Secondary outcomes are breast cancer knowledge, anxiety and depression, and quality of life, as well as treatment delay.

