### Participants

This study will include 106 patients in the cRCT, 53 participants in the Treatment-as-Usual (TAU) control group and 53 participants in the experiment/intervention group. Power calculations suggest a minimum sample size of 41 participants per group (power = 0.80, alpha = .05 two-sided). Taking into account 30% attrition at follow-up, at least 106 participants (53 per group) need to be included. Participants will be recruited from four district hospitals in Bandung, West Java, Indonesia, that are representative for the health care facilities in the different areas in Bandung, Indonesia.

Participants will be new patients (outpatients) who visit the hospital with breast symptoms, which make them suspects of having breast cancer. Patients eligible for the intervention program will be asked to take part in the study when reporting at the district hospitals. The following inclusion criteria will be used: women with age > 18 years, an adequate command of the Indonesian language and no major psychiatric disorder. The last is determined by checking the medical record on a consultation history/record with the Psychiatric Department. Patients who have been seen by psychiatrists are excluded from the study.

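### The model labels level 3 as the intervention and control groups and is fitted separately in each phase, so the variation between the four randomised hospitals is either left out of the error term or rests on 2 degrees of freedom

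*Protocol article*

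**What the plan says.** The Design section describes a cluster-randomised trial "with hospitals as the unit of randomisation (clusters", and adds: "We will include four hospitals in Bandung, Indonesia that have agreed to participate in this study". Two hospitals give PERANTARA in the first period and two give usual care, and the roles are then exchanged. The section justifies the small sample by the fact that each hospital acts as its own control.

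The Abstract states the target of the analysis: "Data will be analysed by hierarchical linear modelling (HLM) to assess differential change over time". The Analysis plan says "a three level model will be used with repeated measures nested in person, and persons nested in clusters", with time at level 1 and the woman at level 2. In parentheses it then identifies the level-3 clusters as the intervention and control groups. The model is to be run separately for the phase before crossover and the phase after it. The same kind of model is planned for the delay questionnaire and for WHOQOL-BREF, EQ-5D 5L, HADS and BCKT.

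The Participants section gives the sample size: "Power calculations suggest a minimum sample size of 41 participants per group" ("power = 0.80, alpha = .05 two-sided"), and "Taking into account 30% attrition at follow-up, at least 106 participants (53 per group) need to be included". It states no effect size, standard deviation or intracluster correlation.

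**The concern.** In a cluster-randomised trial, the treatment effect has to be judged against variation between the randomised units. Three features of the plan work against this.

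- **The level-3 label.** It names the arms, while the Design section says the clusters are hospitals. A level with two units that coincide with the treatment factor cannot supply an error term for that factor.
- **The separate phases.** Fitting each phase alone turns the cross-over into two small parallel comparisons, each of two hospitals against two.
- **The target is change over time.** Even with hospital at level 3, a random hospital intercept is the same at every visit and subtracts out of each woman's change. Hospital differences in change (staff, season, case mix) would then count as noise between women.

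At stake is the false-positive rate. A fluctuation in one or two hospitals during one phase could be reported as an effect of PERANTARA, and the Discussion ties wider implementation to proof of effectiveness.

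**Working it through.** **Inputs from the protocol.** Four hospitals, two per arm in each of two periods; 106 women, 53 per arm; 41 per arm as the minimum; three assessments; two-sided alpha 0.05; power 0.80. **Assumed, because the protocol gives no figure:** the hospital share of the variance of change, ρ (the hospital-by-visit share), set at 0, 0.02, 0.05 and 0.10.

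**1. The plan's own figure.** No effect size is stated, so 41 per group can only be solved backwards: d = (1.960 + 0.842) × √(2/41) = 0.62, a two-sample comparison of independent women. Then 41 × 1.3 = 53.3, which gives the stated 53 per group.

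**2. Women per hospital per phase.** 106 / (4 × 2) = 13.25 recruited; 82 / (4 × 2) = 10.25 at the minimum size.

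**3. Does the hospital intercept cancel?** Write the score as a fixed part for visit and arm, plus a hospital intercept, a woman intercept and a residual. Both intercepts disappear from the difference between two visits. The generalised least squares covariance for 4 hospitals, 13 women each and 3 visits (residual variance 0.5, woman variance 0.45) confirms this:

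| Hospital intercept variance | SE, arm main effect | SE, arm by time at follow-up |
|---|---|---|
| 0 | 0.270 | 0.277 |
| 0.05 | 0.351 | 0.277 |
| 0.5 | 0.757 | 0.277 |
| 5 | 2.252 | 0.277 |

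The right-hand column equals √(2 × 0.5 × (1/26 + 1/26)) = 0.277, the value for 26 individually randomised women per arm.

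**4. Error rate of arm by time within one phase, intercept-only model.** The true variance exceeds the model variance by DE = 1 + (m − 1)ρ, so the nominal 5% test rejects with probability 2Φ(−1.96/√DE).

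| ρ (assumed) | DE, m = 13 | Analytic, m = 13 | Simulated, 13 per hospital | Analytic, m = 10.25 |
|---|---|---|---|---|
| 0 | 1.00 | 5.0% | 4.8-5.2% | 5.0% |
| 0.02 | 1.24 | 7.8% | 7.7-8.4% | 7.2% |
| 0.05 | 1.60 | 12.1% | 12.2-12.4% | 10.5% |
| 0.10 | 2.20 | 18.6% | 19.5-20.3% | 15.8% |

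Simulations used 20,000 null trials per setting.

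**5. The same test with hospital as the unit.** A t-test on hospital means, two against two, has 2 df. It held 4.8-5.2% at every ρ tried. Its critical value is 4.30, so a statistic of 1.96 has p = 0.19.

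**6. Outcomes with one value per woman.** Here the hospital intercept enters the standard error, but its variance is estimated on 2 df per phase. A z-test after REML rejects 8% of the time at an assumed ICC of 0.05 and 11% at 0.10 (13 women per hospital).

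**7. Both phases together.** If each hospital keeps the same pattern of change in both phases, an intercept-only analysis of the stacked phases rejects 3.6-4.9% of the time. The 2-df analysis of within-hospital differences rejects 4.8-5.2%.

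**8. Power of a 2-df test over both phases, with no hospital variation.** Noncentrality 0.62 × √(41/2) = 2.81 against a critical value of 4.30 gives about 35%. The ordinary t-test on 80 df gives 79%. With 53 per group, 0.62 × √(53/2) = 3.19 and the 2-df power is 42%.

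**The case against.** The strongest objection is that the protocol never specifies an intercept-only model. It gives nesting levels, neither states nor excludes a time slope at hospital level, and names no method for standard errors or degrees of freedom. Those details commonly sit in a statistical analysis plan. This stands. A reader might infer that the planned standard errors certainly ignore hospital differences in change, but the text does not go that far. What the protocol does fix is the level-3 label, the target of change over time and the separate phases. A hospital slope, if fitted, would still have its variance estimated on 2 df per phase.

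A reader might also conclude that the p-values will be too small in any event. That depends on hospital variation in change, on which the protocol gives no figure. At zero there is no inflation, and the 19-20% needs the largest share assumed here.

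Nor does the cancellation reach the primary outcome. Diagnosis delay is one interval per woman, and the Procedure section lists no delay form at baseline. A comparison of arms on delay would carry the hospital intercept, and only the small-sample problem applies to it.

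Finally, much of the trouble comes from analysing the phases separately, since stacking them removes the inflation when hospital patterns are stable. That is correct, and separate analysis is what the plan prescribes. Stability across periods is itself an assumption, so pooling alone is not enough.

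**Conclusion.** The point holds in conditional form. The contradiction is firm: hospitals are the clusters in the Design section, the arms are the clusters in the Analysis plan, and the separate-phase rule gives up the within-hospital comparison on which the design rests. On the literal reading, hospital variation enters no standard error. On the favourable reading, with hospital at level 3, tests of arm by time for the repeated secondary outcomes are liberal if change is not allowed to vary by hospital and hospitals do differ in change. The inflation is then modest to fourfold over the assumed range of ρ. For diagnosis delay, a z-test within a phase is liberal because four hospitals leave 2 df. All these sizes rest on assumed shares or ICCs and on about 13 women per hospital per phase. This should be settled before the data are analysed.

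**What to change.** Amend the Analysis plan as follows.

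1. Define level 3 as hospital, and remove the parenthesis that equates the clusters with the arms.
2. Replace the separate-phase analyses with one model for both periods: fixed effects for arm and period, random terms for hospital and hospital-by-period. For the repeated outcomes, also let change over time vary by hospital.
3. Use Kenward-Roger or Satterthwaite degrees of freedom.
4. As a check, reduce each hospital-period to its mean (baseline-adjusted where a baseline exists), form the four within-hospital PERANTARA minus usual-care differences, and analyse them allowing for sequence, with a t reference on 2 df. Variance components from four hospitals are poorly estimated, so this check should be reported beside the model.

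No new patients, hospitals or data are needed, but the cost is more than wording. Intervals will be wider, and power will be below the stated 80%: about 35% for the 2-df analysis with 41 per group at the back-solved d of 0.62, even with no hospital variation. The mixed model may do better, depending on its estimated variances and degrees of freedom. The protocol should state this loss openly.

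### The Design section defines the clusters as hospitals, but the Analysis plan labels the level-3 clusters as the intervention and control groups and names no hospital term

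*Protocol article*

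**What the plan says.** Protocol article, Design: the trial is cluster-randomised "with hospitals as the unit of randomisation (clusters". The number of clusters is fixed: "We will include four hospitals in Bandung, Indonesia that have agreed to participate in this study". Each hospital contributes to both arms, in a randomised order. "In the first period, two hospitals will have the experimental group" and the other two give usual care; the second period reverses this.

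Protocol article, Analysis plan: "a three level model will be used with repeated measures nested in person, and persons nested in clusters". Level 1 is time and level 2 is the person. For the top level the text reads "the clusters (intervention-control group) will be considered as level 3". The section adds that "HLM analysis will be carried out separately for each phase before and after crossover" and that "Demographic variables will be entered as additional predictors including SES, educational levels, and patients’ locations". It carries a similar model over to the secondary outcomes. Hospital is named neither as a level nor as a predictor.

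**The concern.** The word cluster has two meanings in one protocol: four hospitals in the Design section, two arms in the Analysis plan. They are not interchangeable. The arm is the contrast the trial exists to estimate, whereas the hospital is the unit that was randomised and within which outcomes may be correlated. Because every hospital serves in both arms, hospitals are crossed with arms over the whole trial, so arm cannot stand in for hospital as a grouping level.

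An analyst who followed the Analysis plan word for word would code arm as level 3 and leave hospital out. Two things are then at stake: whether the treatment effect can be estimated at all, and whether its standard error reflects the randomisation. The model is the one stated for the primary outcome, so the ambiguity reaches the main result.

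**Working it through.** The plan gives no figure that tests the model structure, so there is nothing to reproduce first. The check compares the sections and then works out what each reading implies.

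**Inputs**
- Four hospitals, two per arm in each of two periods (Design): eight hospital-periods.
- 106 women, 53 per arm; 41 per arm is the calculated minimum; power 0.80, two-sided alpha 0.05 (Participants).
- Women per hospital-period, assuming equal recruitment and no attrition: 106 / 8 = 13.25.
- ICC: not given in the article. Assumed range 0.01 to 0.10, extended to 0.20 in simulation.

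**Reading 1, literal: arm is a random level 3.** There are two units, so only one between-unit difference is observed. A random arm variance τ² and a fixed arm effect would both rest on it and cannot be told apart. If both were fitted, with outcome SD 1 and 41 women per arm, the SE of the arm contrast would be sqrt(2τ² + 2/41):

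| τ (SD) | SE (SD) |
|---|---|
| 0 | 0.22 |
| 0.3 | 0.48 |
| 0.5 | 0.74 |

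The precision would depend on a quantity the data cannot supply.

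**Reading 2: arm tested as an ordinary effect, hospital ignored, one phase at a time.** With m = 13.25, the design effect is DE = 1 + (m − 1) × ICC and the actual alpha is 2 × [1 − Φ(1.96 / sqrt(DE))].

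| ICC (assumed) | DE | Actual alpha |
|---|---|---|
| 0.01 | 1.12 | 0.064 |
| 0.02 | 1.25 | 0.079 |
| 0.05 | 1.61 | 0.123 |
| 0.10 | 2.23 | 0.189 |

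A simulation of one phase (20,000 replicates per setting, two hospitals against two) agrees. At ICC 0.01, 0.05, 0.10 and 0.20 the rejection rate is 0.06, 0.12, 0.20 and 0.31 with 13 women per hospital, and 0.06, 0.11, 0.16 and 0.26 with 10. A test on the four hospital means stays at about 0.05 throughout.

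**Reading 3: the parenthesis is a loose label and level 3 is the hospital.** The model then contains the randomised unit. Analysed per phase, a test on hospital means has 4 − 2 = 2 df. As an illustration, 41 per arm at the stated power and alpha corresponds to a standardised difference of (1.96 + 0.84) × sqrt(2/41) ≈ 0.62; the article does not state this effect. At 0.62 SD with 13 women per hospital, simulated power runs from about 0.25 (ICC 0) to 0.11 (ICC 0.20).

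**Joint analysis of both periods.** Eight hospital-period means, less 1 for the intercept, 3 for hospital, 1 for period and 1 for arm, leave 8 − 6 = 2 residual df.

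**The case against.** The strongest reply is that the Analysis plan nests persons in clusters, the Design section has already defined clusters as hospitals, and within a phase each hospital is wholly intervention or wholly control. The parenthesis could therefore describe the allocation status of hospitals that do sit at level 3. This is a fair reading, and it means the documents do not establish that hospital is left out. It does not remove the contradiction: the text equates the clusters with the groups, and nothing elsewhere corrects it. Patients' locations are listed among demographic variables and cannot be assumed to stand for the hospital attended.

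A reader might infer that the protocol commits the treatment effect to a random level and so has no treatment contrast. The documents do not support this. The Analysis plan never calls the level random, the Abstract speaks of differential change over time, and the Analysis plan itself refers to the effect of the interventions. A full list of fixed effects may properly sit in the statistical analysis plan.

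A reader might also take 6% to 19% as the error rate of the planned analysis. It is not. Those figures belong to Reading 2, a different model from the literal one, and they depend on assumed ICCs, numbers before attrition and separate phases. Under Reading 1 with both terms fitted, the SE grows, which is the conservative direction. In a pooled cross-over analysis each hospital is its own control, so stable hospital differences would largely cancel.

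Finally, the article does not say that hospitals differ in biopsy access or pathology queue. That is plausible for a time-to-diagnosis outcome, but it is an assumption.

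**Conclusion.** The contradiction is certain: the Design section and the Analysis plan disagree on what a cluster is, and this is a statement made wrongly, not detail left to another document. What follows depends on the reading. Taken literally, the randomised unit is omitted and the arm contrast becomes a two-unit level whose variance cannot be separated from the arm effect. If hospitals were meant, the model includes the right unit but the wording misdirects whoever codes it. If hospital is ignored and arm is tested within each phase, type I error rises from 5% to between about 6% and 19% for ICCs of 0.01 to 0.10, assuming equal recruitment of about 13 women per hospital-period. The wording should be corrected before the data are analysed, because it concerns the model for the primary outcome and is carried over to the secondary outcomes.

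**What to change.** Reword the Analysis plan so that the cluster is the hospital and arm is a fixed effect, with an arm-by-time interaction for the repeated secondary outcomes.

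Make the primary analysis a joint analysis of both periods, with fixed effects for arm, period and hospital, a random hospital-by-period term and a small-sample degrees-of-freedom correction. Two details matter:
- Within one phase, hospitals are nested in arm, so a fixed hospital factor is aliased with arm. Adding it to the separate-phase models would not work.
- In the joint model, a fixed hospital-by-period term would use up all eight cells and absorb the arm effect. It must be random.

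Report an analysis of the eight hospital-period means, adjusted for hospital and period, as a check.

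The cost is wider intervals and few degrees of freedom (2 residual df for the hospital-period means). In return, inference respects the randomisation and the cross-over is used as the Design section intends. No new data are required.
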